### Secondary Endpoints

Secondary efficacy parameters are changes in quality of life compared to baseline level. The European Organization for research and treatment of cancer quality of life questionnaire (QOLQ, Bloechle *et al.* 1995 [23], will be used. Also the tolerability of the drug in this patient population will be compared to placebo.

In the experimental part of the study the difference of the QST stimulus are considered secondary efficacy parameters. The experimental baseline recordings will also be compared to published normal values from healthy controls to evaluate general aspects of pain processing in the patient group.

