## Objectives

The present study consists of two parts: one clinical and one involving human experimental pain testing (i.e. QST). In the clinical part the aim is to investigate the effect of pregabalin on clinical pain resulting from chronic pancreatitis. In the clinical part of the study, the primary objective is to understand the effect of pregabalin on the daily pain experienced by patients with chronic pancreatitis.

The experimental part aims at evaluating the effect of pregabalin using QST in controlled and standardized circumstances. In the experimental part of the study the primary objective is to understand the effect of pregabalin on altered pain processing in patients with chronic pancreatitis.

In the clinical part of the study a secondary objective is to understand the effect of pregabalin on the quality of life of patients with chronic pancreatitis. Further secondary objectives are to understand the safety and tolerability of pregabalin in this patient population.

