## Study Period

Seven days prior to the first dose of study drug, the patients will start to score pain levels in a pain diary. The average pain over the previous 24 hours and the worst pain over the previous 24 hours will be assessed using the VAS score. Usage of pain medication will also be recorded in the diary

Visit 2:

Day 1, first dose of study drug:

The patients visit the clinic and are instructed to start the trial medication if laboratory tests are normal. Ahead of the first dose of study drug the patients will undergo multimodal testing. They will have the skin in segments C5, T4, T10, L1 and L4 stimulated electrically. Also deep muscle pain will be assessed on the same places, using pressure stimulation. A cold pressor test is performed on the right hand and the deep muscle pain is measured on the left thigh both before and after the cold pressor test. Pain thresholds will be assessed using visual analogue scales (VAS).

These assessments are done before starting the treatment on Day 1 and on Day 21 + 14 days.

Patients will start the trial medication and score pain levels in the diary with a VAS value for the average pain over the previous 24 hours and a second VAS value for the worst pain over the previous 24 hours. Use of as needs pain medication will also be recorded in the diary.

The duration time of the second visit will be approximately 2 hours.

Telephone interviews

On days 4, 7, 11, 14 and 17 a study nurse or doctor will call the patients to assess the severity and tolerability of any adverse events.

On Day 7 a study nurse or doctor will call the patients to assess the adverse events and to administer the PD-Q and PGIC questionnaires. The dose of study drug will be discussed. Patients with acceptable adverse events will increase the dose to 300 mg BID. Patients experiencing unacceptable adverse events on 150 mg BID will be taken out of the study and will be replaced.

Visit 2:

All patients will visit the centre on day 21 + 14 days.

- Physical examination.
- Concomitant medication
- Questionnaires (QOLQ, mBPI-sf, PD-Q and PGIC) are filled out.
- Blood and urine for haematology, clinical chemistry and urinalysis.
- Pregnancy test (urine) will be done in females not postmenopausal for more than 1 year or not sterile.
- Experimental testing as described in visit 1: pressure and electrical stimulation (skin and muscle).
- Cold pressor test.

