#### Recording of adverse events

Information about adverse events will be collected from the first administration of any investigational product until the end of the study. Adverse events spontaneously reported by the patient and/or in response to an open question “have you had any health problems during the study since previous visit” from the study personnel or revealed by observation will be recorded at each visit from the first administration of any investigational product until the end of the study.

Any deterioration in laboratory values and vital signs need not be reported as AEs. However, abnormal values that meet criteria for an SAE or cause discontinuation of investigational product must be reported as SAE or AE and recorded in the CRF.

The time/date when the AE started and disappeared, maximum intensity, action taken with regard to investigational product, causality rating (yes or no), outcome, if AE caused patient to discontinue the study and whether or not it constitutes an SAE will be reported in the CRF for each AE.

The causality of non-serious AEs (i.e., their relationship to investigational product) will be assessed in the same way as for SAEs.

The intensity rating is defined as:

1 = mild (awareness of sign or symptom, but easily tolerated)

2 = moderate (discomfort sufficient to cause interference with normal activities)

3 = severe (incapacitating, with inability to perform normal activities)

It is important to distinguish between serious and severe AEs. Severity is a measure of intensity whereas seriousness is defined by the criteria as described above. An AE of severe intensity need not necessarily be considered serious. For example, nausea that persists for several hours may be considered severe nausea, but not a SAE.

Any AE not resolved at the last assessment or discontinuation of the study will be followed up within two weeks and thereafter as long as the investigator consider necessary.

The same parameters as for AEs / SAEs will be recorded in the case a SUSAR should occur during the study period.

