### Analysis of Secondary Endpoints

Changes in the secondary endpoints will be analyzed with a non-parametrical test (Mann-Whitney U) Effect of the active treatment is evaluated and presented with 95% confidence intervals.

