## Safety Analysis

No formal analyses are planned for safety data. These data (adverse events, vital signs and routine laboratory tests) will be explored through the use of standard presentations of descriptive statistics.

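### Tolerability is a secondary endpoint under two conflicting analysis rules, one of which cannot be applied to adverse events, and the dropout exclusion may remove the patients who tolerated treatment worst

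*Protocol*

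**What the plan says.** Section 2.1 (Objectives) sets the aim: "Further secondary objectives are to understand the safety and tolerability of pregabalin in this patient population". Section 2.2.2 (Secondary Endpoints) turns it into an endpoint with a comparator: "Also the tolerability of the drug in this patient population will be compared to placebo". It names no variable or summary measure.

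Section 9 has two rules that could apply. Analysis of Secondary Endpoints states "Changes in the secondary endpoints will be analyzed with a non-parametrical test (Mann-Whitney U" and adds "Effect of the active treatment is evaluated and presented with 95% confidence intervals". It makes no exception for tolerability. Safety Analysis states "No formal analyses are planned for safety data". It lists adverse events, vital signs and routine laboratory tests, and says that these "will be explored through the use of standard presentations of descriptive statistics".

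On how tolerability is observed, section 6.2 (Study Period) has staff "call the patients to assess the severity and tolerability of any adverse events" at the telephone interviews. Section 8 (Recording of adverse events) fixes the window: "Information about adverse events will be collected from the first administration of any investigational product until the end of the study". For each event that section also records the maximum intensity, what was done with the study drug, and whether the event led the patient to leave the study.

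On who is analysed, the text under Analysis of Primary Endpoint admits only patients with two weeks or more of study medication, and says that dropouts are replaced and left out of subsequent analyses. No separate safety population is stated.

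**The concern.** A secondary endpoint with a stated comparator should have one analysis rule that can be carried out. This one falls under two rules that ask for different things, and the rule written for secondary endpoints does not fit the data. Whoever writes the analysis plan must depart from one section or the other, and the protocol gives no ground for choosing.

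The population matters more than the choice of test. Patients who leave because they cannot tolerate treatment are the most informative patients for this endpoint. If they are left out, the comparison describes tolerability among those who tolerated treatment, and any excess of withdrawals on pregabalin vanishes from the table. A statement that the drug was well tolerated could then rest on a selected group.

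**Working it through.** The point turns on text, so the relevant statements are set side by side.

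1. **Which rule covers tolerability?** It appears under Secondary Endpoints, so the rule in Analysis of Secondary Endpoints reaches it. It is observed through adverse events (section 6.2), so the Safety Analysis rule reaches it too. The first prescribes a test and an effect estimate with a confidence interval. The second disclaims formal analysis. Neither refers to the other.

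2. **Can the Mann-Whitney rule be carried out?** It operates on changes. A change needs a value before treatment and one after. Adverse events are recorded only from the first dose, so the first value does not exist. Withdrawal and dose reduction also arise only after dosing. Routine laboratory tests are different: the Schedule of Activities takes them at screening and at end of treatment, so they do have a change. But section 6.2 ties tolerability to adverse events, and section 8 says that a worsening laboratory value need not be reported as one unless it meets the seriousness criteria or causes discontinuation of study drug. The rule therefore fits laboratory tests and fails for the data that carry tolerability.

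3. **Can the descriptive rule supply the comparison?** Yes, if the summaries are given by arm. Section 2.2.2 promises a comparison, not a hypothesis test, and section 2.1 speaks of understanding. The Safety Analysis section does not mention arms, but table layout is commonly left to the analysis plan. What this route lacks is the effect estimate and interval that the protocol promises for secondary endpoints.

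4. **Who would be in the comparison?** Section 6.2 takes patients with unacceptable adverse events on 150 mg BID out of the study and replaces them. Section 6.3 (Subject Withdrawal) also replaces withdrawals, until 60 patients have finished. The exclusion of dropouts stands under the primary-endpoint heading, but its wording extends to later analyses, and the next sentence there speaks of all endpoints. Whether it reaches tolerability is undetermined.

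5. **How many patients could this concern?** Section 9.1.1 plans for 60 recruited and 48 completing, an allowance of 60 − 48 = 12 dropouts. Replacement under section 6.3 means that 12 is not a ceiling. The protocol does not say how many dropouts would be due to intolerance or how they would split between arms, so no bias can be calculated.

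**The case against.** The strongest reply is that there is no conflict on an ordinary reading. Section 2.2.2 uses the word changes for quality of life and adds tolerability in a separate sentence. The Mann-Whitney rule also speaks of changes, so it can be taken to cover change scores, with adverse-event data left to the section written for them. Descriptive safety reporting is usual. Adverse-event intensity is graded 1 to 3, so it could be ranked between arms. Withdrawal and action taken with study drug are fields of the adverse-event record, so they fall within the Safety Analysis list.

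Much of this stands. It defeats the inference that the promised comparison is never made, which a reader might draw from the two rules together: a table by arm is a comparison, and ruling out formal analysis does not rule out such a table. It also defeats any claim that withdrawal and dose reduction go unrecorded or unreported.

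It does not remove the point. The protocol nowhere states the exemption that this reading needs. Ranking intensity after dosing would be workable, but it is not an analysis of change. And the reading says nothing about the population. Nor is this only a detail left to the analysis plan: the protocol fixes a rule that does not fit and an exclusion of uncertain reach, and a later document would have to override one or both.

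A reader might also infer that intolerant patients will certainly be dropped. The documents do not establish that, because the exclusion is stated under the primary endpoint.

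**Conclusion.** The point holds as an inconsistency with a practical consequence. Tolerability is a named secondary endpoint compared with placebo. The one rule for secondary endpoints cannot be applied to adverse events, and the safety section plans no formal analysis of them. A descriptive comparison by arm remains open. The more consequential part is conditional: if the dropout exclusion is applied to this endpoint, it removes patients withdrawn for intolerance and can make pregabalin look better tolerated than it was.

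The conclusion assumes that tolerability is measured through adverse events, as section 6.2 indicates, and that the section 9 rules are read as written. No numerical size is attached, because the protocol gives no rates of adverse events, dose reduction or withdrawal by arm. It is worth correcting, but it does not affect the primary analysis.

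**What to change.** In section 9:

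- State that tolerability is exempt from the Mann-Whitney rule.
- State that it is compared by arm in all patients who took at least one dose, including those later withdrawn and replaced, and that the two-week and dropout rules do not apply to it.
- Use data already in the case report form: withdrawal for an adverse event, dose reduction, and adverse events by intensity.
- Report risk differences with 95% confidence intervals. No hypothesis test is needed.
- Add a cross-reference in Safety Analysis, so that its disclaimer of formal analyses no longer contradicts section 2.2.2.

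The exact composition of the measure and the interval method are matters of preference and can go in the analysis plan. The population and the exemption should be in the protocol.

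The cost is a few lines and no new data collection. The small downside is that the intervals will be wide. With about 30 per arm (half of 60), the simple Wald half-width for a difference in proportions is at most 1.96 × √(0.25/30 + 0.25/30) = 0.253, or about 25 percentage points, reached when both proportions are one half. It is narrower at other rates.

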# STUDY DESIGN

This will be a randomized, double-blind, parallel group, placebo-controlled study to investigate the effects of pregabalin on clinical and experimental pain in 60 patients with chronic pancreatitis (30 in Denmark and 30 in the Netherlands).

Participation in the study will involve three outpatient clinic visits, including the screening visit. The second and third outpatient clinic visit will include skin and muscle sensitivity testing. In addition, all subjects will undertake five telephone interviews.

During the study, the patients will be randomized to receive placebo or pregabalin (Lyrica®). The maximum daily dose of pregabalin is 300 mg administered twice per day. Pregabalin is titrated in 2 steps: for the first 3 days 75mg BID is administered. From Day 4 to Day 7, 150 mg BID is administered. From Day 8 to Day 21, 300 mg BID is administered. At the end of the study, patients will undertake a medication taper and will take half their maximum tolerated daily dose of pregabalin for 7 days and then discontinue dosing.

# SUBJECT SELECTION

The investigator will screen sufficient patients to allow 60 patients to complete the study.

## Inclusion Criteria

# Male or female patients between the ages of 18 and 70 years with a diagnosis of chronic pancreatitis, diagnosed using the Marseille-Rome/Cambridge diagnostic criteria (Etemad and Whitcomb, 2001 [24]). Both diabetic and non-diabetic patients will be allowed to enter the study.

### The patients must suffer from chronic abdominal pain typical for pancreatitis, meet the criteria for chronic pain (pain ≥ 3 days per week in at least 3 months) and must consider their pain as severe enough for medical treatment.

# Personally signed and dated informed consent document indicating that the patient has been informed of all pertinent aspects of the trial.

# Patients willing and able to comply with the scheduled visits, treatment plan, laboratory tests and other trial procedures.

## Exclusion Criteria

1. Patients with evidence or history of medical or surgical disease of importance for this study as judged by investigator
2. Presence or history of major depression
3. Patients with previously diagnosed moderate to severe renal impairment. Patients with creatinine values > 2x ULN and/or with a significant change to their normal values should be excluded.
4. Patients with a screening 12-lead ECG demonstrating any of the following: heart rate >100 bpm, QRS duration >120 msec, QTc interval >450 msec, PR interval >210 msec, any clinically significant rhythm abnormality, any evidence of myocardial ischemia or injury.
5. Patients with any clinically significant laboratory abnormalities that in the opinion of the investigator may increase the risk associated with trial participation or may interfere with the interpretation of the trial results.
6. Patients treated with pregabalin (Lyrica®) during the previous 4 months.
7. Treatment with an investigational drug within 4 months preceding the first dose of study medication of importance for this study as judged by investigator.
8. Female patients who are pregnant or lactating, or intend to become pregnant. Male patients who intend to father a child during the course of the study. A pregnancy test will be conducted at visit 1 and 3 to ensure that female patients are not pregnant during the study period.
9. Patients unwilling or unable to comply with the lifestyle guidelines.
10. Patients must not suffer from painful conditions other than chronic pancreatitis.
11. Clinical significant illness within two weeks of participating in this study.
12. Involved in planning or conducting the study.
13. Hypersensitivity to pregabalin or any of its components.

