## Screening

Visit 1; Screening (28 – 7 days before the first dose of study drug):

- Obtain informed consent.
- Physical examination.
- General and specific medical history (including drug/alcohol/tobacco consumption).
- Concomitant medication.
- Questionnaires (QOLQ, mBPI-sf, PD-Q and PGIC) are filled out.
- Blood and urine for hematology, clinical chemistry and urinalysis.
- Pregnancy test (urine) will be done in females not postmenopausal for more than 1 year or not sterile.
- 12-lead ECG.
- Blood pressure and pulse rate (supine and standing). Supine BP/PR should be measured following resting for 5 minutes. Standing BP/PR should be measured following standing for 2 minutes.
- Diary instruction. The patient will start completing the pain diary 7 days prior to the first dose of study drug.
- Experimental testing (training): pressure and electrical stimulation (skin and muscle) as described below.
- Cold pressor test (training) as described below.

Patients fulfilling inclusion and exclusion criteria are randomized and invited to join the study.

The duration time of the first visit will be approximately 4 hours.

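### Exclusion criterion 3 names moderate to severe renal impairment only when already diagnosed, and its one number (creatinine above 2x ULN) does not by itself keep out the same impairment when undiagnosed; the Day 1 laboratory condition conflicts with that limit.

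*Protocol*

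**What the plan says.** Criterion 3 in Protocol section 4.2 has two sentences. The first excludes "Patients with previously diagnosed moderate to severe renal impairment". The second adds a laboratory rule: "Patients with creatinine values > 2x ULN and/or with a significant change to their normal values should be excluded". The significant-change limb carries no number. Criterion 5 excludes "Patients with any clinically significant laboratory abnormalities that in the opinion of the investigator may increase the risk associated with trial participation", and criterion 1 leaves medical history of importance to the investigator.

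Screening (section 6.1) collects "Blood and urine for hematology, clinical chemistry and urinalysis", and the last visit repeats it: "Blood and urine for haematology, clinical chemistry and urinalysis". The Schedule of Activities lists blood chemistry at those two visits only, and weight at the same two. No creatinine clearance, eGFR or renal dose rule appears.

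Patients are randomized if they meet the entry criteria at screening (sections 4.3 and 6.1). On Day 1 they are "instructed to start the trial medication if laboratory tests are normal" (section 6.2). Dosing goes from 75 mg BID to 150 mg BID and then to 300 mg BID from Day 8, with treatment lasting 21 days plus up to 14 more (section 5). Five telephone contacts between Day 4 and Day 17 are described thus: "a study nurse or doctor will call the patients to assess the severity and tolerability of any adverse events". At Day 7, "Patients experiencing unacceptable adverse events on 150 mg BID will be taken out of the study and will be replaced". Section 5 permits step-down to 150 mg BID for intolerance. Section 6.3 permits extra blood tests at the investigator's request and sets 150 mg BID as the lowest end dose.

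**The concern.** Criterion 3 identifies a degree of renal impairment that the investigators do not want in the trial, then makes that exclusion depend on whether somebody diagnosed it earlier. For a patient with no renal diagnosis, the only objective test is creatinine relative to ULN. A fixed multiple of ULN ignores age (and weight), so the same creatinine corresponds to quite different renal function across the eligible range of 18 to 70 years. If 2x ULN lies well inside the moderate-to-severe range, the criterion excludes a patient whose impairment is on file and, on its number, admits another with the same kidneys and no diagnosis.

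A second problem sits beside it. The Day 1 wording asks for normal laboratory tests, whereas the entry criteria tolerate creatinine up to 2x ULN. The two rules disagree for patients between 1x and 2x ULN, and by Day 1 those patients have been randomized.

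**Working it through.** **Inputs from the Protocol.** Creatinine limit above 2x ULN (4.2); ages 18-70 (4.1); 300 mg BID from Day 8, treatment up to Day 35 (section 5).

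**Assumptions, not in the Protocol.** ULN 100, 110 or 120 µmol/L for men and 80, 90 or 100 for women; moderate impairment below 60 and severe below 30 mL/min; weights 45-90 kg. The limit is stated without a derivation, so there is no figure of the plan's own to reproduce.

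**Formulas** (creatinine in mg/dL = µmol/L ÷ 88.4).
- Cockcroft-Gault: (140 − age) × weight ÷ (72 × creatinine), × 0.85 for women.
- CKD-EPI 2021: 142 × min(Scr/k, 1)^a × max(Scr/k, 1)^−1.2 × 0.9938^age, × 1.012 for women; k = 0.9 (men) or 0.7 (women), a = −0.302 or −0.241.

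**One patient worked through.** Man of 45, 70 kg, ULN 100, creatinine at 2x ULN = 200 µmol/L = 2.262 mg/dL, which the number does not exclude.
- Cockcroft-Gault: 95 × 70 ÷ (72 × 2.262) = 40.8 mL/min.
- CKD-EPI: 142 × (2.262/0.9)^−1.2 × 0.9938^45 = 35.5 mL/min/1.73 m2.
- With ULN 120 the same man gives 34.0 and 28.5.

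A 50-year-old, 60 kg woman at 2x ULN gives 28-35 by Cockcroft-Gault and 26-34 by CKD-EPI.

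**Whole grid.** Ages 18-70 in 1-year steps (53 ages) by weights 45-90 kg in 5 kg steps (10 weights) gives 530 cells per sex and ULN.

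| Sex, ULN (µmol/L) | C-G < 60 at 2x | C-G < 30 at 2x | C-G < 60 at 1.5x | CKD-EPI at 2x | CKD-EPI at 1.5x |
|---|---|---|---|---|---|
| Men 100 | 508 | 104 | 369 | 30.4-42.0 | 42.9-59.3 |
| Men 110 | 527 | 158 | 425 | 27.1-37.5 | 38.3-52.9 |
| Men 120 | 530 | 214 | 468 | 24.4-33.7 | 34.5-47.7 |
| Women 80 | 488 | 77 | 328 | 29.7-41.1 | 42.0-58.0 |
| Women 90 | 521 | 135 | 404 | 25.8-35.7 | 36.5-50.4 |
| Women 100 | 530 | 200 | 459 | 22.8-31.4 | 32.1-44.4 |

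- At 2x ULN, Cockcroft-Gault is below 60 in 488/530 to 530/530 cells (92-100%) and below 30 in 77/530 to 214/530 (15-40%). At 1.5x ULN it is below 60 in 328/530 to 468/530 (62-88%).
- CKD-EPI is below 60 at all 53 ages, in both sexes, at both 1.5x and 2x ULN.

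**Sensitivity.**
- The Cockcroft-Gault exceptions at 2x ULN are young, heavy patients: at 18 years and 85 kg, 53-64 for a man and 54-68 for a woman.
- With weights up to 110 kg (742 cells), the share below 60 at 2x ULN is 569/742 to 710/742 (77-96%).
- With a slightly lower male ULN of 1.1 mg/dL (about 97 µmol/L), an 18-year-old man at 1.5x ULN reaches 61.3 by CKD-EPI. At 2x ULN he is at 43.4.

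**Day 1 rule beside the entry rule.** Chemistry is scheduled before dosing only at screening, so the Day 1 condition must refer to those results. For creatinine between 1x and 2x ULN, the numeric limit in criterion 3 says eligible, and sections 4.3 and 6.1 then randomize the patient; Day 1 read literally says do not start drug. Read to mean that no exclusionary abnormality is present, the two rules agree, but Day 1 adds no renal filter.

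**Exposure.** Day 8 to Day 35 inclusive is 35 − 8 + 1 = 28 days at 300 mg BID at most.

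**The case against.** The strongest objection is the Day 1 sentence. Taken as written, nobody with creatinine above 1x ULN starts drug, and most of the exposure described here disappears. That stands as far as it goes: the text supports this reading at least as well as the looser one. But on that reading the 2x ULN limit has little purpose and randomized patients are refused drug, so the text still needs repair. It would also not catch low clearance at a normal creatinine: a 70-year-old, 60 kg woman at 1.0 mg/dL has a Cockcroft-Gault clearance of 49.6 mL/min.

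Second, a diagnosis rule plus a separate laboratory cap is a coherent design, and nothing says that 2x ULN was meant to represent moderate impairment. That is fair. The point is narrower: whatever the cap was meant to do, it does not extend the named exclusion to undiagnosed patients.

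Third, creatinine near 2x ULN with no renal diagnosis is an obvious candidate for criterion 5, and investigator judgement is a legitimate eligibility mechanism. This also stands. One cannot infer that such patients will be enrolled, only that the number does not stop them. The significant-change limb helps only where an earlier value exists. The calls, the Day 7 removal, step-down and discretionary blood tests are real safeguards, but none is a renal limit.

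Some stronger readings are not supported:
- A reader might take 92-100% as the share of patients affected. It is an unweighted share of grid cells at one creatinine value.
- A reader might infer 35 days at 300 mg BID. The maximum is 28, in the pregabalin arm only.
- A reader might infer a demonstrated drug hazard. The Protocol does not say how renal function alters pregabalin risk, so the point rests on criterion 3's own choice of exclusion.
- A reader might infer bias in the primary comparison. A patient refused drug would be replaced (section 6.3) and would not meet the two-week rule for analysis.

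**Conclusion.** The point holds as a minor-to-moderate safety and consistency matter. The exclusion of moderate to severe renal impairment depends on a prior diagnosis or on individual judgement, because the only number lies well inside the range that the criterion names. By CKD-EPI this is so at every eligible age for creatinine of 1.5 to 2x ULN (23-59 mL/min/1.73 m2). By Cockcroft-Gault it is so for nearly all ages and weights at 2x ULN.

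The size rests on the assumed ULN ranges, the 60 and 30 cut-offs and, for Cockcroft-Gault, the weights; varying them changes the shares but not the conclusion at 2x ULN. How many patients fall in this range cannot be known from the Protocol. Whether they would be dosed depends on how Day 1 is read, and that ambiguity is itself part of the finding.

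**What to change.** In criterion 3, delete the prior-diagnosis qualifier and replace the 2x ULN cap with an eGFR limit by one named formula: for example, exclude CKD-EPI below 60 mL/min/1.73 m2, or the sponsor's own cut-off for moderate. It is computed from screening creatinine, age and sex. Keep the significant-change limb. On Day 1, make the start of medication conditional on screening laboratory results meeting the entry criteria.

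The cost is two reworded sentences, one calculation from data already collected at Visit 1, and some added screen failures. The number of failures depends on the formula. At creatinine exactly 1x ULN, a Cockcroft-Gault limit of 60 would already exclude 77 to 214 of 530 cells (15-40%), the older and lighter patients with normal creatinine. CKD-EPI at 1x ULN is below 60 at none of the 53 ages for ULN 100 or 110 in men or 80 in women, and at 2 of 53 for ULN 90 in women. With a high ULN it is below 60 at 11 of 53 ages (men, 120) and 23 of 53 (women, 100). CKD-EPI is therefore the cheaper choice unless the laboratory's ULN is high.
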